### Statistical power and Sample size

Power analyses were conducted using the partial eta-squared (η_p_^2^) from the repeated measures ANOVAs run for the pilot study. Analyses were based on a sample size of 180 (90 per arm) with a conservative estimate of 30% drop-out. Further, it is recognized that there is the possibility of a placebo effect not observed in the pilot study due to the provision of an active control group. Placebo effects of as large as a 30% reduction in hot flash frequencies and hot flash severity scores have been reported (Sloan et al., 2001). Thus, the calculations reported here are based on a sample size of 126 with effect sizes 30% smaller than those from the pilot study.

An overall experiment-wise alpha of 0.05 will be used, with a Dunn/Bonferroni correction to adjust the error rate for individual analyses. Twenty-one separate analyses are planned (8 for Aim 1, 8 for Aim 2, 5 for Aim 3). Thus, these sample size calculations are based on α = 0.00238 (0.05/21).

Power calculations were conducted using pilot data, analyzed using repeated measures ANOVAs with one between-subjects and one within-subjects variable. Calculations were conducted using G*Power and focused on the interaction term from these analyses. G*Power takes into account the expected effect size (η_p_^2^, reduced by 30%), alpha (0.00238), desired power (0.90), correlation between pre- and post-test, and sphericity. The sample size needed for 0.90 power based on these calculations (CES-D, η_p_^2 ^= 0.0672, *r *= 0.492, pre-post) was 72 (sample size calculations using other dependent variables were smaller). Given a sample size of 180, with a 30% drop out/missing data rate, power would be 0.99 for this comparison. Thus, this study is adequately powered even if a higher than anticipated drop out rate occurs, or if missing data reduces the *N *for some of the analyses.

Participant demographic characteristics will be analyzed using descriptive statistics, including baseline characteristics, averages, and related confidence intervals. Hot flash scores and frequencies will be plotted over the study period. The hot-flash score, being a measure of severity and frequency, is determined by multiplying the daily frequency of hot flashes by their severity (Perez et al., 2004). Analysis will be completed to fully examine and explore the data and to test the hypotheses.

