Primary analyses will be conducted using a mixed model approach, with each dependent variable analyzed separately as a pretest-posttest control group design with one within-subjects variable (pre-post) and one between-subjects variable (experimental-control). Composites will be used for analyses with multiple scales (e.g., a single sleep composite will be used).

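### The primary pre-post by arm interaction is valid but makes inefficient use of the baseline; adjusting for baseline would cut the variance by about 19–25% for CES-D, at no cost

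*Protocol article*

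**What the plan says.** The last paragraph of *Statistical power and Sample size* sets the primary model. It begins "Primary analyses will be conducted using a mixed model approach" and continues with "each dependent variable analyzed separately as a pretest-posttest control group design with one within-subjects variable (pre-post) and one between-subjects variable (experimental-control"). The baseline measurement is thus the first level of a repeated outcome. The text names no baseline covariate and does not say that the arms share a baseline mean.

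The word interaction comes from the power paragraphs of the same section: "Calculations were conducted using G*Power and focused on the interaction term from these analyses". The inputs stated there are:
- The CES-D effect, correlation and resulting N: partial eta-squared "0.0672, *r *= 0.492, pre-post) was 72".
- A discount to "effect sizes 30% smaller than those from the pilot study".
- The significance level: "these sample size calculations are based on α = 0.00238 (0.05/21").
- The remaining G*Power settings, including "desired power (0.90), correlation between pre- and post-test, and sphericity".
- Enrolment and loss: "Analyses were based on a sample size of 180 (90 per arm) with a conservative estimate of 30% drop-out", which leaves 126 for analysis. The stated power at that number is 0.99.

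*Randomization* says that the 7-day baseline is collected before the arm is assigned.

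**The concern.** With two arms and two occasions, the interaction asks whether the mean change differs between arms. It lets the baseline means differ by arm, although assignment after baseline makes them equal in expectation. Subtracting the whole baseline value is the best use of it only when the pre-post correlation is 1. At a correlation near one half, the subtraction adds about as much noise as it removes, whereas regression on baseline removes only the part that predicts follow-up. What is at stake is precision, not validity. The plan tests each outcome at 0.05/21, expects up to 30% loss, and allows for a placebo response not seen in the pilot, so precision that needs no new data is worth having.

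**Working it through.** **Inputs** (all from *Statistical power and Sample size*): partial eta-squared 0.0672, r = 0.492, alpha 0.00238, target power 0.90, 126 completers (63 per arm) out of 180 (90 per arm). Let σ² be the outcome variance, taken as equal before and after treatment.

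**1. Reproduce the plan's figures.** G*Power's repeated-measures interaction with two groups and two occasions uses f² = η²/(1 − η²) and λ = f² × N × 2/(1 − r), with 1 and N − 2 degrees of freedom.
- f² = 0.0672/0.9328 = 0.0720.
- The smallest even N with power of at least 0.90 is 72 (power 0.908), which matches the article.
- At N = 126 the power is 0.998; the article says 0.99.
- Cutting 0.0672 by a further 30% gives N = 102, so 0.0672 already includes the 30% discount.

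**2. Variance of the arm contrast, complete pairs.** The interaction F equals t² from a two-sample test on post minus pre.
- Change score: 2(1 − r)σ² = 2 × 0.508 σ² = 1.016 σ².
- Follow-up adjusted for baseline: (1 − r²)σ² = (1 − 0.242)σ² = 0.758 σ².
- Ratio: 0.758/1.016 = (1 + r)/2 = 0.746, a reduction of 25.4%.
- A simulation of 10,000 trials with 63 per arm gave 25.0%, which includes the cost of estimating the slope.
- Equivalent size: 126/0.746 ≈ 169 completers under the change-score test.

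**3. Variance if a likelihood mixed model keeps every baseline.** Take 90 baselines and 63 follow-up values per arm, missing completely at random, with baseline means free to differ by arm. Per arm:
- As planned: (1 − r²)/63 + (1 − r)²/90 = 0.01203 + 0.00287 = 0.01490 σ².
- With baseline adjustment: (1 − r²)/63 = 0.01203 σ².
- Reduction: 1 − 0.01203/0.01490 = 19%.

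**4. Other correlations.** The complete-pairs reduction is 1 − (1 + r)/2:

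| r | Reduction |
|---|---|
| 0.3 | 35% |
| 0.492 (CES-D) | 25% |
| 0.6 | 20% |
| 0.7 | 15% |
| 0.8 | 10% |

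**5. Sample size and power on the plan's own inputs.** The G*Power formula implies an interaction of √(16 × 0.0720) = 1.07 SD. With the baseline-adjusted variance and N − 3 degrees of freedom, N for 0.90 power is 54 instead of 72. At N = 72, power rises from 0.908 to 0.978. At N = 126 it is already 0.998, so adjustment can add almost nothing there.

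**6. A conditional case.** Suppose, as an assumption, that the pilot partial eta-squared already reflects r through the within-subject error term. Then λ = f² × N = 0.0720 × 126 = 9.08, and the implied interaction is √(8 × 0.508 × 0.0720) = 0.54 SD. At alpha 0.00238 and 126 completers, power would be 0.47 for the interaction and 0.65 with baseline adjustment.

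**The case against.** The strongest reply is that nothing here is an error. The interaction test is valid under randomisation, the power calculation uses the same test, and on the plan's figures power is 0.99 after dropout. That stands as to validity and consistency, and it limits the finding to efficiency. It does not remove it, because the article states the form of the model instead of leaving it to a later plan.

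A second reply is that a mixed model is not a plain change-score test. This stands in part: with dropouts' baselines retained, the gain for CES-D falls from 25% to 19%. A mixed model with a common baseline mean would be about as efficient as covariate adjustment, but the text does not describe one.

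A reader might also infer more than the documents support:
- *That real power is below one half.* The article states 0.99, and its inputs reproduce 0.998. The figure of 0.47 needs the assumption in step 6. The article's statement that the effect sizes come from pilot repeated-measures ANOVAs makes that assumption plausible, but it is a separate question about the G*Power input.
- *That all 21 analyses lose 25%.* The correlation of 0.492 is for CES-D; none is given for hot flash frequency or score. The article gives only counts by aim (8, 8 and 5) and also lists moderators, so it does not show that all 21 are plain pre-post arm comparisons.
- *That recruiting women with frequent hot flashes biases the comparison by regression to the mean.* Selection precedes randomisation and affects both arms alike, so it cancels in the contrast. Chance baseline imbalance is already counted in 2(1 − r).

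**Conclusion.** The point holds as an efficiency finding. The primary test treats baseline as an outcome level and gives up precision that the trial's own baseline data could supply. For CES-D the loss corresponds to a variance cut of about 25% with complete pairs, or about 19% under a likelihood mixed model with 30% of follow-up values missing completely at random. Both figures assume equal variances before and after treatment and r = 0.492. For other outcomes the size is unknown: 35% to 15% for r from 0.3 to 0.7 with complete pairs.

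On the plan's own effect size the practical gain at 126 completers is negligible. It becomes material if the true effect is smaller than assumed. The planned analysis would not give an invalid answer.

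**What to change.** In the primary-analysis paragraph, replace the description of the model with one sentence: for each pre-post comparison of the arms, the primary estimate is the between-arm difference at follow-up, adjusted for the baseline value of the same measure. A mixed model with a common baseline mean across arms serves equally well. One of the two should be named in advance.

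The number of tests and the alpha of 0.00238 stay as they are, and no further analysis on a transformed scale is needed for this purpose. The stated N of 72 can remain, described as calculated for the less efficient interaction test.

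The cost is a wording change. No new data, visits or participants are required, and *Current Status of Trial* says accrual was still under way, so the change could be made before any comparison of the arms.

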**Methods/design:**

A sample of 180 post-menopausal women will be randomly assigned to either a 5-session Hypnosis Intervention or 5-session structured-attention control with 12 week follow-up. The present study will compare hypnosis to a structured-attention control in reducing hot flashes (perceived and physiologically monitored) in post-menopausal women in a randomized clinical trial. Outcomes will be hot flashes (self-report daily diaries; physiological monitoring; Hot Flash Related Daily Interference Scale), anxiety (State-Trait Anxiety Inventory; Hospital Anxiety and Depression Scale (HADS); anxiety visual analog scale (VAS rating); depression (Center for Epidemiologic Studies Depression Scale), sexual functioning (Sexual Activity Questionnaire), sleep quality (Pittsburgh Sleep Quality Index) and cortisol.

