### Effect Measures

Outcomes will be hot flashes (self-report daily diaries; physiological monitoring; Hot Flash Related Daily Interference Scale), anxiety (State-Trait Anxiety Inventory; Hospital Anxiety and Depression Scale (HADS); anxiety visual analog scale (VAS rating); depression (Center for Epidemiologic Studies Depression Scale), sexual functioning (Sexual Activity Questionnaire), sleep quality (Pittsburgh Sleep Quality Index) and cortisol; moderators will be cognitive expectancies (VAS ratings) and hypnotizability (Stanford Hypnotic Susceptibility Scale-Form C). A figure representing the schedule of collection is provided [Figure 2].

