### Salivary cortisol

Salivary cortisol samples will be collected four times in the same day by participants during the week before the first session (baseline) and after completing approximately five sessions of the hypnosis intervention or structured-attention control. Instructions will be provided to participants upon receipt of the cortisol materials. Pre- and post-session salivary cortisol samples will also be collected at the participants' first session with the research therapist. Salivary cortisol samples will be assayed with a time-resolved immunoassay with a cortisolbiotin conjugate as a tracer. Total cortisol produced over a day will be measured by calculating the area-under-the-curve (AUC). This represents the total volume of cortisol secretion over the day. We will also examine cortisol levels at each time point averaged across the areas under the curve and mean diurnal and nocturnal levels will be compared and the presence of circadian rhythmicity will be evaluated [39].

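### The primary pre-post contrast is tied to no named visit, although a 12-week follow-up runs beyond about five weekly sessions; name the primary occasion and use one baseline-adjusted longitudinal model.

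*Protocol article*

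**What the plan says.** Under *Statistical power and Sample size*, the primary analyses use a mixed model, run separately for each dependent variable as "a pretest-posttest control group design with one within-subjects variable (pre-post") and "one between-subjects variable (experimental-control"). The power calculation in the same section targets the interaction from that pre-post layout. It allows for losses "with a conservative estimate of 30% drop-out" and tests at 0.05/21: "Twenty-one separate analyses are planned (8 for Aim 1, 8 for Aim 2, 5 for Aim 3"). The content of the three aims is not described.

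On timing, the abstract gives "5-session structured-attention control with 12 week follow-up". *Randomization* has assignments opened at the week 1 visit, and both intervention sections describe approximately weekly sessions. Only *Salivary cortisol* places a post-treatment collection in words: "after completing approximately five sessions of the hypnosis intervention or structured-attention control". For the other measures, *Effect Measures* refers to a figure: "A figure representing the schedule of collection is provided [Figure 2". The only other stated use of data over time is descriptive: "Hot flash scores and frequencies will be plotted over the study period". *Data Quality and Data Monitoring* has the monitoring board check completion of both phases of the study, without defining the phases.

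**The concern.** Five approximately weekly sessions from week 1 end at about week 5. Whether 12 weeks counts total time on study or time after treatment, follow-up outlasts treatment. A two-level factor holds one post value, and the text does not say which.

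Two things are at stake. First, an end-of-treatment contrast estimates the immediate effect and a week-12 contrast the sustained effect, so a reader cannot tell which one the primary result will be. Second, the plan sets a strict per-test alpha. If two occasions are measured and the choice stays open until data are seen, that alpha no longer holds.

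**Working it through.** **1. Is the two-level factor really the working model?** Inputs from *Statistical power and Sample size*: partial eta-squared 0.0672 (taken as already reduced by 30%), r = 0.492, alpha = 0.05/21 = 0.00238, two arms, N = 180 less 30% = 126.

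G*Power within-between interaction, with m time levels and sphericity:
- f² = 0.0672/(1 − 0.0672) = 0.0720
- noncentrality = N·m·f²/(1 − r)
- df = (m − 1) and (N − 2)(m − 1)

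| Time levels m | N | Power |
|---|---|---|
| 2 | 72 | 0.908 |
| 2 | 126 | 0.998 |
| 3 | 54 | 0.904 |

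The plan's N of 72 reproduces with m = 2, and its stated power of 0.99 at 126 is consistent. With m = 3 the requirement would be 54. The plan therefore rests on one pre and one post value.

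**2. Error if the occasion is chosen freely.** The two-sided critical value at 0.00238 is 3.038. The per-test error is P(|Z1| > 3.038 or |Z2| > 3.038) for two correlated statistics. The correlation is not in the document, so a range is shown.

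| Assumed correlation | Per-test error | × 21 analyses |
|---|---|---|
| 0.5 | 0.0046 | 0.097 |
| 0.7 | 0.0044 | 0.092 |
| 0.8 | 0.0041 | 0.086 |

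The upper bound is 2 × 0.00238 = 0.0048. The last column bounds the experiment-wise error against the stated 0.05, if the choice were open in all 21 analyses.

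**3. Gain from baseline adjustment with one post value.** Take unit variance at both times, r = 0.492, 126 women with both values and 54 with baseline only, losses at random and equal across arms. Variances below are in units proportional to that of the between-arm contrast.
- Planned two-level mixed model, which uses the baseline-only women: (1 − r²)/126 + (1 − r)²/180 = 0.7579/126 + 0.2581/180 = 0.00602 + 0.00143 = 0.00745. Effective N for the pre-post change is 2(1 − r)/0.00745 = 1.016/0.00745, or about 136.
- Baseline as covariate, or baseline means constrained equal: (1 − r²)/126 = 0.00602.
- Reduction: 1 − 0.00602/0.00745 = 19%.

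**4. Gain from a second post occasion.** Assume that 27 of the 54 lost women have an end-of-treatment value, that the two post values correlate q, and that each correlates 0.492 with baseline. The partial correlation is p = (q − r²)/(1 − r²), and the variance is (1 − r²)·[(1 − p²)/126 + p²/153].

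| q | p | Variance | Further cut against 0.00602 |
|---|---|---|---|
| 0.5 | 0.34 | 0.00589 | 2% |
| 0.7 | 0.60 | 0.00563 | 6% |
| 0.8 | 0.74 | 0.00544 | 10% |

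**5. Is sample size a barrier?** Not on the plan's own effect-size inputs. Testing both occasions in every analysis (42 tests, alpha 0.00119) needs N = 78 and has power 0.995 at 126. The fix below does not need those extra tests.

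**The case against.** The strongest reply is that two post-treatment assessments are inferred, not stated. No section lists both an end-of-treatment and a week-12 value for any outcome, and the schedule sits in a figure that is missing only because the text was extracted from a PDF. This stands as a limit: the error figures apply only if both occasions are measured and the choice is left open. It does not remove the point, because the analysis text itself states a primary model and ties *post* to no visit.

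A reader might infer three stronger things that the article does not support.
- **That an assessment is thrown away.** The pre-post wording governs primary analyses only, and a second occasion may sit among the 21 analyses or in secondary work.
- **That the trial cannot show whether benefit lasts.** If *post* is week 12, the primary contrast addresses exactly that.
- **That women without the chosen post value contribute nothing.** The plan names a mixed model and randomisation follows baseline collection, so a likelihood fit uses baseline-only women and is valid under missing-at-random given baseline. The comparator for any precision gain is therefore an effective N of about 136, not 126.

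It may also be said that baseline as covariate is mere preference and drops women with no post value. The 19% reduction answers the first part. The second is correct for a plain covariate model; constraining the baseline means to be equal keeps all randomised women.

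**Conclusion.** The point holds in limited form. The primary contrast is two-level and attached to no named visit for outcomes other than cortisol, in a trial whose follow-up outlasts treatment. Whether two post-treatment occasions are measured cannot be confirmed from the text.

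If they are, an open choice would roughly double the per-test error (1.7 to 1.9 times 0.00238 at assumed correlations of 0.8 to 0.5). Separately, the planned interaction is less precise than a baseline-adjusted contrast: about 19% of the variance is given up. That figure rests on the plan's r of 0.492 (reported for the depression scale), equal variances and 30% loss at random. The extra 2-10% from a second occasion rests on assumed missingness and correlations and is secondary. This should be settled before analysis; it does not threaten the sample size as the plan calculates it.

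**What to change.** The sponsor should name, for each outcome and before any outcome data are examined by arm, the single post-treatment occasion that forms the primary contrast. The choice between end of treatment and week 12 is the sponsor's.

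Replace the pre-post interaction with one mixed model per outcome containing arm, time (all post-treatment occasions), arm-by-time and baseline as covariate. Alternatively, fit baseline as an outcome with means constrained equal across arms, which keeps all randomised women. Use an unstructured covariance. Take the primary contrast at the named occasion from this model, and report any other occasion from the same model as secondary. Cortisol keeps its single post-treatment value. State which of the 21 analyses, if any, concern a second occasion.

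The cost is analysis wording only: no new data and no change in sample size.

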### Data Quality and Data Monitoring

All data (with the exception of VAS ratings of anxiety, and pre and post measurements of resting heart rate and blood pressure) will be collected by the Research Coordinator and Data Coordinator separate from the therapists providing intervention. The Data Coordinator will oversee data entry. To assure quality, data will be entered into a data base twice by doctoral Students in Psychology at Baylor University or other assigned personnel who will be blinded as to the participants' assignment. The data will then be sent to a biostatistician and checked for consistency and completeness. Any inconsistency or incompleteness will be addressed by the Research Coordinator, Data Coordinator and PI for accuracy. A data safety and monitoring plan has been developed for this study. The P.I. in conjunction with the biostatistician or other assigned personnel will check the data for completeness and quality on a quarterly basis. Once the data has been entered into a data base and data quality has been assured the data base will be subjected to further analyses. As required by NCCAM/NIH, a DSMB will be selected and will periodically review the adverse events and the collected data. Within the 5 year study duration, we expect the DSMB to meet at least annually. The meetings will serve to establish whether the study is accruing appropriately, whether the data collection is running smoothly, whether unexpected toxicities are present, and whether patients are completing both phases of the study. At a minimum, the DSMB will meet at least annually and within 7 days of any serious adverse events.

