### Randomization

After the 7-day baseline data have been collected, participants may return the completed daily diary, Biolog^® ^3991 monitor, Bahr monitor and cortisol samples. Between week 0 and week 1 visits, the Research Coordinator will contact the Data Coordinator who will provide random assignment for the participant, and this assignment will be placed in a sealed envelope that will not be opened until the visit at week 1. Random assignment will be made sequentially from a confidential computer-generated list of permuted blocks of varying size. The list is generated to provide equal probabilities to the study arms. The study participants will be randomly assigned by the Data Coordinator to either the hypnosis intervention or to a structured-attention control group. An overview of the chronology of the study is provided graphically [Figure 1].

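### The role that makes each random assignment also shares in collecting the outcome data and settling data queries, and only the data-entry staff are said to be blinded

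*Protocol article*

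**What the plan says.** Two sections of the protocol article describe the duties.

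*Randomization.* Between the week 0 and week 1 visits, "the Research Coordinator will contact the Data Coordinator who will provide random assignment for the participant". The section says again who assigns: "The study participants will be randomly assigned by the Data Coordinator to either the hypnosis intervention or to a structured-attention control group". On the source of assignments: "Random assignment will be made sequentially from a confidential computer-generated list of permuted blocks of varying size". On concealment: "this assignment will be placed in a sealed envelope that will not be opened until the visit at week 1". The keeper of the list is not named.

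*Data Quality and Data Monitoring.* Data "will be collected by the Research Coordinator and Data Coordinator separate from the therapists providing intervention". The exception is stated as "with the exception of VAS ratings of anxiety, and pre and post measurements of resting heart rate and blood pressure". On entry: "The Data Coordinator will oversee data entry". Keying is done twice by personnel described as blinded to assignment, after which a biostatistician checks the data for consistency and completeness. On what that check turns up: "Any inconsistency or incompleteness will be addressed by the Research Coordinator, Data Coordinator and PI for accuracy".

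**The concern.** The plan evidently regards knowledge of the arm as a threat: it keeps data collection apart from the therapists and blinds the people who key the data. Yet the role that necessarily knows the arms, because it assigns them, is placed on both sides of the blinded step. Before entry, it shares in collecting diaries, questionnaires, recordings and samples. After entry, it shares in deciding what becomes of records that are incomplete or do not agree.

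At stake is the comparability of the outcome record between arms. If missing diary days are chased harder in one arm, or doubtful entries are accepted more readily in one arm, the comparison can shift without any keying error. The hot-flash score multiplies daily frequency by severity (Statistical power and Sample size), so a decision on an unclear diary entry feeds directly into a main outcome. Participants know which sessions they attend, and the article claims no participant blinding. Masking on the staff side is therefore a protection that the sponsor can still arrange.

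**Working it through.** No arithmetic applies: the point depends on no alpha, effect size, drop-out rate or sample size, and the plan gives no figure to reproduce. The check sets the duties of each role side by side.

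| Step | Who does it | Section | Said to be blinded? |
|---|---|---|---|
| Providing the assignment | Data Coordinator | Randomization | No; knows the arm by doing it |
| Collecting data (except anxiety VAS, heart rate, blood pressure) | Research Coordinator and Data Coordinator | Data Quality and Data Monitoring | Not stated |
| Overseeing data entry | Data Coordinator | Data Quality and Data Monitoring | Not stated |
| Keying the data twice | Doctoral students or other assigned personnel | Data Quality and Data Monitoring | Yes |
| Checking consistency and completeness | Biostatistician | Data Quality and Data Monitoring | Not stated |
| Resolving what the check finds | Research Coordinator, Data Coordinator, PI | Data Quality and Data Monitoring | Not stated |

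1. **Overlap.** The Data Coordinator appears in four of the six rows: assignment, collection, oversight of entry, and query resolution.

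2. **Does the sealed envelope mask this role?** No. The Data Coordinator supplies the assignment before it is sealed. The envelope conceals it from others until week 1, but not from the person who provided it.

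3. **Does blinded double entry cover the gap?** Only in part. It guards against transcription error and biased keying. It cannot correct what was done to a record before keying (prompting, follow-up, accepting a partial diary) or what is decided about a discrepancy afterwards. The Data Coordinator takes part in both.

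4. **Does sharing query resolution cover the gap?** Not by itself. Two other roles take part, but the article does not say that either is blinded.

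5. **Does separation from the therapists cover the gap?** It removes a different source of bias, that of the person delivering the intervention. It says nothing about the person who assigned it.

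6. **Which outcomes are exposed, and how?** Under Effect Measures, Sternal Skin Conductance Monitoring and Salivary cortisol, the outcomes are self-completed diaries and scales, device recordings and assayed samples. The article describes no rating by a coordinator. What remains is contact with participants, effort spent on follow-up, and the handling of incomplete or inconsistent records. Anxiety VAS, heart rate and blood pressure lie outside the point, because the coordinators do not collect them.

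**The case against.** The strongest reply is that the outcomes leave little room for an arm-aware coordinator. Women complete their own diaries and questionnaires, a device records skin conductance, and cortisol is assayed. For self-report the participant is in effect the assessor, and she is unmasked whatever the staff know. The plan also keeps therapists away from collection, blinds the double entry, has a biostatistician find the discrepancies, sends them to three roles jointly, and adds a quarterly check of completeness and quality. A journal article may also omit masking arrangements that sit in a working manual.

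Much of this stands. It rules out rater bias as the mechanism and shows that the Data Coordinator does not act alone. It does not remove the routes through contact, follow-up and query decisions. Nor is the point one of missing detail: the article positively gives these duties to one role. If query masking already exists, one sentence saying so would largely settle the matter.

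A reader might infer three stronger things that the document does not support.

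- *That allocation concealment is compromised.* The article does not say who holds the list or who meets women at baseline. It does say that assignment follows the 7-day baseline, runs sequentially from a confidential list with varying block sizes, and is sealed until week 1. Foreknowledge of the next assignment is conjecture; knowledge of assignments already made is not.
- *That up to 30% of the data would pass through arm-aware decisions.* The 30% in Statistical power and Sample size is a conservative drop-out and missing-data allowance for the power calculation. It is neither a forecast nor a volume of queries.
- *That staff blinding is broken for diary completion.* Women fill in the diaries themselves; only the later handling is exposed.

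**Conclusion.** The point holds in a limited form. One role assigns women to arms and also shares in collecting nearly all outcome data, oversees their entry and shares in resolving imperfect records. The only blinding stated is that of the data-entry personnel, which covers neither what precedes keying nor what follows it.

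The size of any bias cannot be given from the document: there is no count of queries, no rule for settling them and no split of collection work between the two coordinators. No sample size, power or alpha figure changes. The article shows an opportunity for influence, not that any occurred.

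The conclusion assumes that the person who provides an assignment knows it, which follows directly from the description, and that no masking of collection or queries exists beyond what the article states. It does not depend on the Data Coordinator holding the whole list. The change is worth making, because the remedy is cheap and the trial was still accruing when the article was prepared.

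**What to change.** Reallocate duties among existing staff and state the result in the protocol:

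- The role that issues assignments takes no part in collecting outcomes or resolving queries on them.
- Everyone who settles queries, including the Research Coordinator and the PI, works on records from which the arm code has been removed.
- Each decision on an incomplete or inconsistent record is logged before unmasking.

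The second element is essential. Moving collection to the Research Coordinator does not secure masking on its own, because neither that role nor the PI is said to be blinded and the envelope is opened at week 1. If collection staff may learn the arm from participants, query decisions on code-free records still protect the last step.

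The cost is somewhat more collection work for the Research Coordinator and a small data-handling step to strip the arm code. No new staff, measurements or sample size are needed.
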